## Abstract

**Background:**

The COVID-19 pandemic has caused devastating morbidity and mortality globally, and poses an unprecedented threat to economic growth. The global rollout of vaccines has been met with socioeconomic disparities, impeding the global effort in infection prevention and severity reduction. The development and evaluation of candidate vaccines against COVID-19 that overcome logistical, social, and economic challenges are highly needed. Here, a trial protocol is presented to assess the safety, tolerability, and immunogenicity of the TANCoV-1.3.20 SARS-CoV-2 vaccine among healthy participants who were SARS-CoV-2 negative in Tanzania.

**Objective:**

The primary objective of this study was to evaluate the safety and tolerability of the TANCoV-1.3.20 nasal SARS-CoV-2 vaccine in healthy adult participants in Tanzania. The secondary objectives included the assessment of vaccine-induced humoral and cellular immune responses, and preliminary evaluation of dose-related immunogenicity.

**Methods:**

TANCoV-1 is a phase 1/2a double-blinded, randomized controlled trial conducted in the Dar es Salaam and Mbeya regions of Tanzania. A total of 150 healthy participants were planned to be recruited and randomized at a 1:1:1 ratio to receive a TANCoV-1.3.20 vaccination dose of 100 µL with or without a booster, or 200 µL without a booster. Each dose group was planned to contain an intervention arm and a control arm in a 1:1 ratio. In general, 75 participants were planned to be assigned to the experimental arm, and another 75 participants were planned to be assigned to the standard arm. Participant recruitment was expected to take 6 months, with follow-up for 6 months post vaccination. The trial has two primary end points: (1) safety, as ascertained by the incidence of adverse events, and (2) immunogenicity, which involves local, humoral, and cellular immune responses. The trial enrolled healthy individuals aged between 18 and 45 years, who provided written informed consent and met all the inclusion criteria per the protocol. The data will be analyzed using Stata (version 14; StataCorp LLC). Findings will be reported according to the CONSORT (Consolidated Standards of Reporting Trials) guidelines.

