##### Secondary End Points: Immunogenicity End Points

The secondary end points are (1) the proportion of participants with a specific TANCoV-1.3.20 humoral response, (2) the magnitude of the specific cellular response to TANCoV-1.3.20, (3) the proportion of participants with serum-neutralizing antibody responses to TANCoV-1.3.20, and (4) the characteristics of the humoral response produced by the TANCoV-1.3.20 vaccine.

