### Sample Size Estimation

The sample size for this noninferiority clinical trial was calculated to compare the proportion of seroconversion on day 28 between participants receiving the investigational vaccine TANCoV-1.3.20 and those receiving the standard Sinopharm COVID-19 vaccine. On the basis of prior studies and seroconversion data from the Tanzanian setting, we assumed an 88% seroconversion rate for the control group (Sinopharm) and expected a 90% seroconversion rate in the experimental group. A noninferiority margin of 20 percentage points was set, meaning that TANCoV-1.3.20 would be considered noninferior if its seroconversion rate was not more than 20% lower than that of Sinopharm. Using a 1-sided significance level (α) of .05, 80% power (1−β), and a 1:1 allocation ratio (experimental: control), the required total sample size was estimated at 50 participants per group. The study includes 3 study groups, with 25 participants per arm, resulting in a total planned sample size of 150 participants. This sample size provides sufficient power to establish noninferiority if the lower bound of the CI for the difference in seroconversion remains above the preset margin. The calculation assumes binomial proportions and follows standard methods for noninferiority designs in parallel trials [30].

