#### Data Analysis

The data will be analyzed using Stata (version 14; StataCorp LLC). Findings will be reported according to the CONSORT (Consolidated Standards of Reporting Trials) guidelines. Primary analyses will be based on the intention-to-treat population, and secondary analyses will be based on the per-protocol population.

The primary end point will be analyzed via a marginal Poisson regression model fitted using generalized estimating equations, with the logarithm of follow-up time included as an offset and the study arm as the predictor. The incidence rate ratio and its 95% CI will be derived from the Poisson regression model. Incidence rates will also be calculated as the number of incident cases divided by the person-time in years, with person-time calculated from randomization to (1) the study end at 6 months after the last participant enrollment and (2) death or the time last seen if lost to follow-up. In addition, absolute effects on the primary endpoint will be summarized using risk differences (events per 1000 person-years) and their 95% CIs, estimated from the model-based predicted rates in each arm.

In a secondary analysis of the primary end point, we will adjust the Poisson regression model for covariates, defined a priori (age and sex). Each protocol analysis will be performed and defined according to reported adherence to the intended allocation. Subgroup analysis of the primary end point will also be performed via the Poisson model on the prespecified subgroup variables (age and sex).

Other secondary outcomes will be analyzed using generalized linear models, depending on their distributions. The mean difference with its 95% CI will be derived for a continuous outcome, and the odds ratio with its 95% CI will be estimated for a binary outcome.

AEs will be summarized according to the number and percentage of individuals experiencing AEs.

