### Anticipated Reporting

Final analyses are expected to be completed by December 2026, and the primary results are expected to be submitted for publication in 2025. Study findings will be reported following CONSORT guidelines, including results for the primary end points (incidence of AEs and immunogenicity outcomes reflecting local, humoral, and cellular immune responses).

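### Immunogenicity is ranked both primary and secondary, and the day-28 noninferiority comparison that sizes the trial is neither listed in that form nor matched by any stated analysis

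*Protocol article*

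**What the plan says.** **Rank of immunogenicity.** Two places in the protocol article make it primary:

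- Abstract, Methods: "The trial has two primary end points: (1) safety, as ascertained by the incidence of adverse events, and (2) immunogenicity".
- Anticipated Reporting, in the body of the article: "including results for the primary end points (incidence of AEs and immunogenicity outcomes reflecting local, humoral, and cellular immune responses".

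Two places make it secondary:

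- Abstract, Objective: "The primary objective of this study was to evaluate the safety and tolerability", followed by "The secondary objectives included the assessment of vaccine-induced humoral and cellular immune responses".
- The end-point section of the Methods puts only safety under its primary heading and lists the immune measures under "Secondary End Points: Immunogenicity End Points".

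**Sizing.** Sample Size Estimation holds the only calculation. The size "was calculated to compare the proportion of seroconversion on day 28" between TANCoV-1.3.20 and Sinopharm. It assumes 88% for control and 90% for experimental, with a 20-point noninferiority margin, one-sided α of .05, 80% power and 1:1 allocation. This leads to 25 per arm, 50 per group and 150 in total. Noninferiority is judged by the lower confidence bound for the difference in seroconversion.

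**Analysis.** Data Analysis begins: "The primary end point will be analyzed via a marginal Poisson regression model". It then gives binary secondary outcomes an odds ratio with a 95% CI. Immunogenicity Analysis defines a seroconversion rate and names paired t tests, Wilcoxon signed-rank tests or one-way ANOVA for comparisons. It gives no margin.

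**The concern.** The comparison that justifies the size of the trial has no settled standing. A reader cannot tell whether noninferiority to Sinopharm will be a main conclusion or a supportive one, because the article supports both.

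The comparison is also not named where it should be. The Objective paragraph of the Abstract and the six objectives in the Methods mention no comparison with Sinopharm; objective 4 compares the TANCoV-1.3.20 regimens. The end-point list contains proportions with a humoral or neutralizing response to TANCoV-1.3.20, but no day-28 time point and no contrast with control.

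Nor does settling the rank lead to the sized test, since the analysis sections do not describe it. What is at stake is the standing of the trial's only powered result and the interval by which it will be judged.

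**Working it through.** **1. Reproduce the stated size.** Inputs from Sample Size Estimation: control 0.88, experimental 0.90, margin 0.20, one-sided α .05 (z = 1.645), power 80% (z = 0.842), 1:1 allocation. Method: unpooled normal approximation.

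- Variance sum: 0.88 × 0.12 + 0.90 × 0.10 = 0.1056 + 0.0900 = 0.1956.
- Distance from the margin: 0.20 + 0.02 = 0.22.
- n per arm = (1.645 + 0.842)² × 0.1956 / 0.22² ≈ 25.0, so 25.
- Per group 2 × 25 = 50; over three groups 150. This matches the article.
- SE at 25 per arm = √(0.1956/25) = 0.0884. Power = Φ(0.22/0.0884 − 1.645) = Φ(0.842) = 80.0%.

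The figure is sound. The 25 per arm is justified by this test, and no safety end point is sized.

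**2. Compare the sized test with the stated analyses.**

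| Section | Effect measure | Interval or test | Margin |
|---|---|---|---|
| Sample Size Estimation | difference in proportions | lower CI bound, one-sided .05 | 20 points |
| Data Analysis, binary secondary outcomes | odds ratio | 95% CI | none |
| Immunogenicity Analysis | seroconversion rate, GMT | t test, Wilcoxon, ANOVA | none |

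An odds ratio cannot be read directly against a 20-point margin, because the equivalent odds ratio depends on the control rate:

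- Control 88%, lower limit 68%: (0.68/0.32)/(0.88/0.12) = 0.29.
- Control 90%, lower limit 70%: (0.70/0.30)/(0.90/0.10) = 0.26.

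**3. Effect of the confidence level.** One-sided .05 corresponds to the lower bound of a two-sided 90% CI. A two-sided 95% CI corresponds to one-sided .025 (z = 1.960).

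- Power at 25 per arm = Φ(0.22/0.0884 − 1.960) = Φ(0.527) = 70.1%.
- n for 80% power = (1.960 + 0.842)² × 0.1956 / 0.22² = 31.7, so 32 per arm, 64 per group, 192 in total.
- Smallest observed difference that passes, at the planning variances: −0.20 + 1.645 × 0.0884 = −5.5 points with a 90% CI; −0.20 + 1.960 × 0.0884 = −2.7 points with a 95% CI. A result between these values is noninferior under one rule and not under the other.

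**4. Actual enrolment.** The article reports 169 enrolled. If these were spread evenly (169/6 ≈ 28 per arm) and all evaluable, power would be 83.8% with a 90% CI and 74.9% with a 95% CI. Study Groups attributes the increase to sample quality, so the evaluable number per arm is not known.

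**The case against.** The strongest reply is that much of this can be read sensibly. Three stronger inferences are tempting, and the document does not support them.

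- **The Poisson model would fall on titers and seroconversion.** A reader might infer this if immunogenicity is primary. But Data Analysis speaks of one primary end point, incident cases and person-time, the Abstract defines safety by adverse-event incidence, and immunogenicity has its own analysis section. The model is plainly meant for adverse events.
- **Two primary end points inflate the type I error.** That needs two tests, either of which could carry a success claim. Only noninferiority has a success criterion; adverse-event rates are estimated and compared with no margin or success rule.
- **A primary safety end point without a size rationale is an error.** A phase 1/2a trial that estimates safety need not be powered on it. Sizing on a secondary end point is unusual but not wrong in itself.

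Two qualifications also stand. The first listed secondary end point, a proportion with a humoral response, partly covers seroconversion; what is absent is day 28 and the contrast with Sinopharm. And the reference in Immunogenicity Analysis to primary endpoints may only mean the main measures within that analysis, so it is weak evidence on rank.

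The full protocol or analysis plan may settle the rank. That does not remove a contradiction within the published text. Nor does condensation explain it: two of the conflicting statements are adjacent paragraphs of one abstract, and the body conflicts with itself as well.

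**Conclusion.** The concern holds as an inconsistency of rank, definition and analysis, not as a fault in the sample-size arithmetic. Immunogenicity is primary in two places and secondary in two. The sized comparison is not listed in the form that was sized, and no analysis section delivers it.

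The measurable part is the interval. Under the sizing rule, power at 25 per arm is 80.0%. If the 95% level in Data Analysis were carried over to the difference in proportions, it would be 70.1%, with 32 per arm (192 in total) needed for 80%. These figures rest on the planned rates of 88% and 90%, the normal approximation and all 25 per arm being evaluable.

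A reader might infer that the rank has been, or will be, chosen after seeing results. The document does not show that. It shows only that the article leaves both options open while recruitment is complete and analyses are described as underway. It does not say whether unblinding has occurred.

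**What to change.** Give immunogenicity one rank in the Abstract (Objective and Methods), the end-point list, Immunogenicity Analysis and Anticipated Reporting, and date the correction relative to unblinding. Either choice is coherent:

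- **(a) Secondary.** Correct the Abstract (Methods) and Anticipated Reporting. State that the size rests on a secondary end point, so that noninferiority is a supportive conclusion.
- **(b) Co-primary.** Limit it to day-28 seroconversion, with safety estimated rather than tested. This raises the rank of an end point after recruitment has closed, so the date matters most here.

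Under either choice:

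1. List day-28 seroconversion versus Sinopharm in the objectives and end points, with its antigen (which Sample Size Estimation does not name) and the group comparison or comparisons it covers.
2. State its analysis as the difference in proportions, with the lower bound of a two-sided 90% CI compared with −20 points. If a 95% CI is kept, restate the power at 25 per arm as about 70%.
3. State that the Poisson model in Data Analysis applies to adverse events only.

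The cost is rewording, plus the lower stated power if the 95% interval is kept. No new participants are needed for the 90% rule. The downside is that immune measures outside the named end point can no longer be presented as primary results.

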**Results:**

This paper describes the study protocol. Recruitment was completed in February 2024, following regulatory and ethical approvals. Safety and immunogenicity data will be analyzed after the completion of participants’ follow-ups. Laboratory testing is ongoing, and data cleaning and statistical analyses are underway. Safety and immunogenicity outcomes will be analyzed after all follow-up visits and laboratory assays have been completed.

**Conclusions:**

This randomized clinical trial in an African context will provide valuable data that can be used to ensure the future availability of safe, cost-effective, and environmentally accustomed effective vaccines. Furthermore, the findings of this trial will help increase public awareness and acceptance of COVID-19 vaccines, contributing to efforts to combat the COVID-19 pandemic.

## Introduction

### COVID-19 and Its Origin

COVID-19 is a respiratory illness caused by SARS-CoV-2, a virus that was first reported in Wuhan, China, in 2019 [1]. This disease was declared a pandemic by the World Health Organization (WHO) in 2020 because of the large number of cases reported globally [2,3]. As of July 9, 2023, there were more than 767 million confirmed cases and more than 6.9 million deaths reported globally, with the majority of cases coming from Europe, the United States, and the Western Pacific. However, Africa has reported only 1% of cases and 3% of deaths globally, although this may be due to concerns about inadequate and unreliable testing facilities. According to the WHO COVID-19 dashboard, as of July 5, 2023, there were 43,078 confirmed COVID-19 cases and 846 deaths in Tanzania [4-6].

SARS-CoV-2 is a virus that belongs to the beta-genera of coronaviruses, which include other human coronaviruses, such as SARS-CoV and Middle East respiratory syndrome coronavirus (MERS-CoV) [2]. A phylogenetic analysis of several SARS-CoV-2 isolates revealed that they are genetically closely related to coronaviruses that have been isolated from bat populations, indicating that SARS-CoV-2 is a zoonotic virus that has made its way into the human population. However, as of 2020, zoonotic linkages have not been established [7]. Coronaviruses are a large family of viruses that cause a range of illnesses, ranging from mild to severe, including the common cold and more serious diseases, such as SARS-CoV, MERS-CoV, and SARS-CoV-2, which have had alarming impacts on humans [8-10].

The SARS-CoV-2 virus has evolved and changed due to genetic selection caused by mutations and recombination [11]. A high rate of mutation in SARS-CoV-2 is associated with the rapid emergence of new viral variants. For example, the alpha variant first appeared in Great Britain in November 2020, followed by the delta variant, which dominated the summer of 2021, and at the end of 2021, the omicron variant emerged and dominated the world [12].

The recommended preventive measures for SARS-CoV-2 are threefold. First, infection control should be practiced in areas where community transmission is widespread. Second, personal preventive measures are recommended to prevent community transmission. Third, serial viral testing is recommended in long-term care facilities to identify cases, isolate positive cases, quarantine contacts, and thus prevent outbreaks. Overall, adherence to these measures can reduce the risk of SARS-CoV-2 transmission [13-17].

### SARS-CoV-2 Vaccines

Vaccines have been crucial tools in the prevention of viral infections for a long time. The development of vaccines to prevent SARS-CoV-2 infection is seen as a highly promising strategy for mitigating the COVID-19 pandemic. By the end of 2020, multiple vaccines had become available for use, and over 40 candidate vaccines were being tested in human trials, with more than 150 in preclinical trials [18]. Several platforms have been used to develop COVID-19 vaccines through traditional methods, such as inactivated or live attenuated viruses, as well as modern platforms, such as recombinant proteins and vectors [19].

### COVID-19 Vaccine Availability and Delivery in Africa

According to the US Food and Drug Administration (FDA) and the WHO, to be licensed and approved for use, a COVID-19 vaccine must meet a minimum efficacy criterion of at least 50%, with a lower bound of the 95% CI at 30% [20,21]. To determine efficacy, phase 3 trials are being conducted with a follow-up period of 6 months, and a minimum of 30,000 participants are needed. Once phase III trials demonstrate safety and efficacy according to the minimum efficacy criteria, the FDA makes decisions on vaccine licensure. Regulatory bodies in Canada and European countries also take similar approaches to licensing their vaccines [20]. However, whether Africa can meet these licensing requirements remains unknown. Vaccine manufacturing requires sophisticated technological resources. Although the production of an African-made COVID-19 vaccine is encouraged to address the pandemic effectively, many countries’ vaccine manufacturing capabilities need to be improved with government funding [22-24], which is meagerly the case among most African governments. The storage and handling requirements of vaccines pose operational challenges, particularly in resource-limited settings, such as Tanzania. For example, the Pfizer vaccine requires ultracold storage in specialized freezers. Additionally, the WHO recommends discarding open vials 6 hours after opening or at the end of the immunization session, whichever comes first. The need for vials used to hold vaccines may also pose supply chain issues in Africa. This highlights the need for more African-made vaccines that can consider storage and handling challenges, in addition to other economic, logistical, and sociocultural issues [25]. Owing to limited vaccine supplies, recipient groups in the beginning were prioritized based on the risks of acquiring infection, severe morbidity and mortality, negative societal impact, and transmission to others. The WHO has proposed a framework that takes into account global equity concerns, including the assurance of vaccine access to low- and middle-income countries [21].

The development of vaccines within African countries could help increase their availability and accessibility in the region. One of the initiatives in place is the development of the TANCoV-1.3.20 vaccine candidate in Tanzania.

### The TANCoV-1.3.20 Vaccine

The TANCoV-1.3.20 is a live attenuated vaccine derived from a novel strain of avian coronavirus (ACoV). The virus was isolated in 2020 in Tanzania from chickens identified with ACoV disease, and confirmed by polymerase chain reaction using spike protein–encoding gene (S1) primers, which revealed a band of 213 base pairs. Preliminary results have shown that the strain TANCoV-1.3.20 cross-reacted with and was neutralized by antibodies from individuals who had recovered from SARS-CoV-2 infection. Results from the virus neutralization test revealed that the geometric mean titer (GMT) of neutralizing antibodies detected in individuals recovered from SARS-CoV-2 infection was log_2_ 6.5.

It has been shown that protective immunity provoked by ACoV is associated with the major structural protein, spike (S) glycoprotein, which induces neutralizing antibodies [26]. Neutralizing antibodies against the S-protein have been targeted for the development of protective vaccines and therapies against SARS-CoV-2 infection worldwide.

It has been proposed that the ACoV vaccine may be used against SARS-CoV-1 [27]. Moreover, ACoV does not cause disease in humans [28].

The TANCoV 1.3.20 vaccine is thermostable, can be stored at ambient temperatures, and can be administered via the intranasal route while maintaining safety and stability. Owing to its route of administration, there is no need to use needles or syringes, thereby avoiding needle-stick injuries and disposal challenges. It is in liquid form with a light green color. The dose of the vaccine per nasal drop (25 µL) has a titer of 10^6^ embryo infective dose (EID_50_) mL^–1^.

On the basis of preclinical results from animal models of inbred mice, rabbits, and pigs, the TANCoV-1.3.20 vaccine is tolerable, safe, and immunogenic.

## Methods

### Study Design and Settings

This is a phase 1/2a double-blinded, randomized controlled phase trial that aims to assess the safety, tolerability, and immunogenicity of the TANCoV-1.3.20 SARS-CoV-2 vaccine candidate among healthy participants in the Dar es Salaam and Mbeya regions of Tanzania. In Dar es Salaam, participants are recruited from the general population and communities such as the police and prison forces, while in Mbeya, participants are recruited from the general population.

For the social component, a convergent mixed methods study using separate and parallel administrations of semistructured in-depth interviews and interviewer-administered questionnaires is embedded in the trial. The design enables the generation of an in-depth understanding of aspects of the trial that promote participants’ acceptance of trial participation. The theoretical framework of acceptability (TFA) will be used to guide the assessment of acceptability. The TFA consists of 7 component constructs, namely, affective attitude, burden, ethicality, intervention coherence, opportunity costs, perceived effectiveness, and self-efficacy [29].

A list of all enrolled participants per site, including their demographics and scheduled visits, will be developed to aid in purposive sampling and the scheduling of appointments for informed consent and data collection during follow-up visits.

